## Abstract

**Background:**

Substance Use Disorder (SUD) persists as a significant public health challenge worldwide, with an estimated prevalence of approximately 10-15% across the global populace. This condition is characterized by a notably high risk of lapses and relapses, even subsequent to treatment interventions. Mobile health interventions, owing to their widespread accessibility, emerge as a promising approach to diminish the risk of relapse post-treatment and to broaden the scope of care, especially in regions with a scarcity of trained medical professionals.

**Method:**

This study is designed to assess the effectiveness of mobile interventions in mitigating cravings and preventing lapses among individuals diagnosed with SUD. Employing a two-armed, randomized controlled trial framework, the study will evaluate a self-administered psychological intervention delivered through a mobile application, Nałogometr 2.0. Over a period of three months, participants will engage with intervention modules that primarily incorporate mindfulness techniques and Cognitive Behavioral Therapy (CBT) principles. Ecological Momentary Assessment (EMA) will be utilized to gather longitudinal data on a range of variables that are indicative of craving intensity and the risk of lapse. In addition to this, a monthly-administered battery of questionnaires will be employed to gauge the severity of substance dependence, as well as to measure levels of anxiety, depression, and overall life satisfaction.

**Results:**

Results will be submitted for publication in peer-reviewed journals.

**Clinical trial registration:**

https://clinicaltrials.gov/, identifier [NCT05730504].

## Introduction

Substance Use Disorder (SUD) continues to be a grave concern for public health, affecting an estimated 10-15% of the global population (1). The 5-th edition of the Diagnostic and Statistical Manual of Mental Disorders (DSM-5) lists 11 criteria for an SUD diagnosis, falling into four categories. Criteria 1-4 are related to the impaired control of substance use (consuming the substance in larger quantities and for longer than intended, continuing usage despite the desire to cut down or regulate use, spending a great deal of time on obtaining, using, and recovering from the substance, and experiencing cravings, defined as a persistent desire to use substance). Criteria 5-7 refer to an impairment of social life due to substance use (like inability to fulfill major social and work obligations due to substance use, continuing usage despite it causing significant interpersonal problems, and reduction or discontinuation of social activities because of substance use). Criteria 8 and 9 describe risky use – using the substance in unsafe environments, and persistent usage despite knowing that it may cause physical or psychological problems. Criteria 10 and 11 are physiological: experiencing the buildup of tolerance (requiring increasingly higher doses to achieve the same level of intoxication) and symptoms of withdrawal (adverse effects occuring when substance levels in the body decrease).

Among European countries, Eastern European region has the highest rates of alcohol consumption. Latvia, with 13.19 litres of pure alcohol consumed per capita yearly, is a country with the highest alcohol consumption in the region. In Poland, the yearly consumption is estimated at 11.89 litres of pure alcohol per capita, which is well above recommended use.

Even though in United States less alcohol is consumed (9.97 litres per capita), alcohol dependence rates are similar. It is estimated that 13.9% of US populations struggles with alcohol dependence, which makes US the 5th most affected country (higher rates of alcohol dependence are found in Hungary, Russia, Belarus and Latvia).

In Poland, the most common forms of addiction are alcohol dependence, impacting roughly 12.8% of population (2), and nicotine dependence, affecting around 21% (3). The prevalence of addiction to other psychoactive substances is more difficult to quantify, largely due to legal constraints; however, based on the percentage of individuals seeking treatment, amphetamine (33%) and cannabis (32.8%) are the leading substances of illicit use, followed by opioids (15%) and cocaine (3.1%) (4). The high global prevalence, coupled with the considerable risk of relapse—approximately 40-80% of individuals in recovery return to substance use following treatment completion (5, 6) underscores the particularly chronic and intractable nature of SUD. Morover, a vast majority of those affected, potentially up to 80%, never engage in any form of therapy (7, 8). Contributing factors include a scarcity of medical professionals skilled in treating addiction disorders and patients’ tendency to minimize the severity of their issues. Furthermore, the societal stigma associated with substance use often serves as a barrier, deterring individuals from seeking the help they need (9, 10).

Cognitive Behavioral Therapy (CBT) and mindfulness-based interventions have been established as the most effective methods for treating a range of addictions (11–14). CBT, in particular, demonstrates substantial benefits in addiction treatment as it offers a multifaceted approach by addressing mood disturbances and addiction cravings through the reconstruction of maladaptive beliefs and behaviors, proving its effectiveness in conjunction with pharmacotherapy within clinical settings (15, 16). Additionally, the advent of computer-assisted CBT presents a promising alternative, capitalizing on the ubiquity of computers and internet-enabled mobile devices. Notably, research underscores the utility of a six-module computer-assisted CBT program as a valuable supplement to traditional substance use disorder therapy (17). This innovative solution not only exhibits cost-effectiveness compared to standard CBT but also obviates the necessity for continuous clinician access, marking a significant stride in addiction treatment accessibility.

Mindfulness meditation is recognized for its efficacy in diminishing psychological distress and rumination, as well as reducing symptoms of anxiety and enhancing positive affect (18). Standardized mindfulness interventions have also been shown to significantly alleviate emotional distress and symptoms associated with certain mental disorders (19). Techniques intrinsic to mindfulness, such as focused attention and open monitoring, aim to develop and refine skills in attentional reorientation, metacognition, cognitive reappraisal, and inhibitory control. These competencies are central in effectively managing cravings and maladaptive addictive behaviors (20). Mindfulness-Based Interventions (MBIs) are structured to promote awareness of one’s moment-to-moment experiences, including emotions, thoughts, bodily sensations, and surrounding stimuli. These interventions have demonstrated success in treating SUDs, as they target fundamental mechanisms of addiction by enhancing the recognition and comprehension of triggers, emotions, and thoughts tied to addictive behaviors. MBI programs integrate mindfulness practices to aid in coping with the symptoms of SUD, for instance, by maintaining a mindful presence during experiences of craving in everyday life (21). MBIs have shown greater effectiveness in mitigating withdrawal symptoms and cravings, as well as reducing negative substance use outcomes, in comparison to other psychotherapeutic modalities. However, in terms of substance use frequency and relapse rates, Cognitive Behavioral Therapy (CBT), MBIs, and treatment as usual (*ie, education on substance use, participating in 12-step process-orientated group, or medical management including pharmacotherapy and weekly individual counseling sessions*) did not show significant differences (22).

The emerging sector of mobile health (mHealth) technologies presents a potential strategy to tackle challenges faced by patients with SUD, particularly the heightened risk of relapse following treatment completion. Mobile health encompasses a spectrum of mobile technologies aimed at bolstering health, including mental health (23). Interventions delivered via smartphones are increasingly popular due to their widespread accessibility (24). mHealth interventions have shown promise in augmenting the long-term outcomes of SUD treatments and may play a role in mitigating issues related to social stigma and the insufficient availability of healthcare professionals (25, 26).

Psychological interventions disseminated through mobile technology may offer beneficial therapeutic effects in managing addiction, offering cost-effectiveness and increased accessibility since they do not necessitate continuous contact with a healthcare professional (27, 28). These interventions can be integrated as complementary treatments alongside conventional SUD therapy and pharmacological approaches (17, 29). Additionally, mobile interventions grounded in Cognitive Behavioral Therapy (CBT) can function as supportive measures post-treatment, assisting in the reduction of relapse risk and bolstering therapeutic gains (30).

Mobile technologies facilitate the efficient collection of data via Ecological Momentary Assessment (EMA) (31). EMA entails the real-time and recurrent sampling of participants’ current moods, behaviors, and experiences as they occur in the individual’s natural environment, throughout their daily life (32). While traditional surveys are employed in addiction research, they are often limited to single-time measurements and may not adequately capture the dynamics and fluctuations in behavior (33). EMA not only serves as a research tool for scientists but also supports participants in developing self-monitoring and self- management skills (34), which are recognized as beneficial for behavioral modification in individuals coping with addiction (35–37).

Although interest in mobile health (mHealth) technologies is surging, with over 300,000 applications available in digital marketplaces (38), only a limited number have undergone clinical evaluation before being released for widespread usage (39). Despite many of these applications employing scientific terminology to substantiate their benefits, the evidence supporting them is frequently of poor quality or altogether absent (40). Nonetheless, those apps that have been subject to scientific scrutiny have demonstrated promising outcomes, with positive effects on health-related behaviors (41). The inherent characteristics of mHealth interventions render them an encouraging support mechanism for patients with Substance use disorder (SUD) — given their remote delivery, they can be utilized on demand, providing immediate assistance and support amid episodes of increased craving. Consequently, mHealth solutions are particularly valuable for relapse prevention among patients who have concluded formal treatment. The persistent and considerable risk of relapse following treatment poses a significant challenge in the management of addictive disorders, and mHealth interventions offer a viable approach due to their convenience, ease of use, and broad accessibility. Moreover, mHealth solutions hold the potential to overcome barriers to accessing therapy, such as social stigma, while remaining cost-effective and widely available.

There are some mobile apps dedicated to reducing substance use already available on the market (e.g. *Quitzilla, Drinker’s Helper, Helpic*), but only a few of them have been scientifically tested – examples of such apps include *Drink Less* (42) for alcohol use or *Assess, Plan, Track, Tips (APTT;*
43
*)* and *Norwegian Cannabis Cessation app* (44) for cannabis use. Their features include tracking day-to-day substance usage in a form of sobriety calendars, as well as psychoeducational content on substance dependence and psychological components on recognizing and dealing with triggers and craving.

Given these insights, it becomes imperative to provide patients with addictive disorders access to scientifically validated, evidence-based mobile health (mHealth) solutions. This paper introduces a protocol for a two-arm randomized controlled trial (RCT) designed to evaluate the effectiveness of self-guided, mobile-delivered CBT- and mindfulness-based psychological interventions. The goal is to enhance the post-therapy effects of SUD treatment and aid in the prevention of lapses. These interventions will be administered through the Nałogometr 2.0 app, a science-based mHealth application developed to decrease craving intensity and the risk of lapses in individuals experiencing problematic substance use or those diagnosed with SUD.

The Nałogometr 2.0 app incorporates multiple self-guided psychological interventions predominantly rooted in cognitive behavioral therapy and mindfulness. It offers users the autonomy to interact with any module at their convenience without adhering to a predetermined regimen, thereby affording greater flexibility in tailoring psychological interventions to meet their current needs. Beyond delivering psychological intervention modules, the app is also engineered to foster self-monitoring and self-management by enabling users to self-record their behaviors, and mental and physiological states through Ecological Momentary Assessment (EMA). Additionally, users receive personalized feedback in response to their input.

## Materials and methods

### Aim

The aim of the study is to evaluate the effectiveness of mobile interventions in reducing craving and lapses in patients with substance use disorder.

### Study design

The study was pre-registered within the Open Science Framework (OSF) repository: https://osf.io/z4xqd.

A two-arm participant-blinded randomized control trial will be conducted via a mobile app. The study will compare an intervention experimental condition with a waitlist control condition.

Throughout the duration of the study, participants assigned to the experimental group will have access to self-guided psychological interventions.

Participants will be asked to complete daily EMA questions, as well as questionnaire battery assessments at multiple timepoints: 1) at baseline – in the first week, following onboarding questionnaire; 2) after one month; 3) after two months; 4) after three months.

### Participants

The research will be conducted in collaboration with MONAR and AKMED, Polish organizations responsible for overseeing numerous addiction treatment clinics and centers, as well as other independent institutions. Recruitment of participants will target clinical patients who are undergoing either in-patient or out-patient treatment for Substance Use Disorder (SUD). For the in-patient cohort, the study will include individuals who are in the final stage of their therapy, specifically those expected to conclude their treatment within a maximum of 4 weeks but not fewer than 5 days. Eligible participants must be adults, aged 18 years or older, and must possess fluency in Polish. Moreover, in light of the study’s methodology, enrollment will be limited to users of iOS or Android smartphones.

Participants will be recruited into three groups: 1) Patients with alcohol addiction, 2) Patients with cross-addiction (alcohol and stimulants), 3) Patients with cannabis addiction. We plan on recruiting 150 participants with alcohol addiction, 150 participants with cross-addiction, and ~100 participants with cannabis addiction, due to lower availability of CUD therapeutic programs in Poland – and subsequently, less patients finishing therapy.

Each participant will be assigned to either experimental or control condition upon logging in to the mobile app for the first time.

### Sample size calculation

A simulation-based power analysis was performed to determine the sample size, premised on the use of a linear mixed-effects model with subject-level random intercepts and a small effect size of the intervention. This effect size assumption was informed by literature on the efficacy of mobile interventions in mitigating addictive behaviors (for a review, see 25). The simulation indicated that a minimum of 360 participants would be necessary to achieve an 80% power threshold for detecting a significant group effect. The sampling strategy has been devised to capture maximal demographic variance within the sample, with particular attention to characteristics such as gender, age, geographic location, and socioeconomic status.

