### Measures

During the onboarding process—initiated at the first login—participants will be prompted to provide sociodemographic information, including gender, age, place of residence, and details of their addiction profile. They will also respond to questions about their history of substance use, encompassing aspects like the substance involved, duration of use, frequency, treatment history, and periods of abstinence. A series of standardized questionnaires (refer to **Table 1** for an overview) will be employed to gather data on a range of psychological variables. These questionnaire batteries will be administered at one, two, and three months into the study, facilitating the collection of longitudinal data.

**Table 1 T1:** Measures used in questionnaire assessment.

	Group 1 (cross-addiction)		Group 2 (alcohol addiction)		Group 3 (cannabis addiction)	
Measures	Baseline	Monthly assessments	Baseline	Monthly assessments	Baseline	Monthly assessments
*Socio-demographic questions*	**x**		**x**		**x**	
*Onboarding questions*	**x**		**x**		**x**	
Substance use-related measures						
*Dependence severity* (Screener)	**x**	**x**	**x**	**x**	**x**	**x**
*Substance dependence* (SDS)	**x**	**x**	**x**	**x**	**x**	**x**
*Alcohol dependence* (AUDIT)	**x**	**x**	**x**	**x**	**x**	**x**
*Stimulants dependence* (DUDIT)	**x**	**x**				
*Cannabis dependence* (CUDIT-R)					**x**	**x**
Psychological functioning measures						
*Anxiety and depression* (HADS)	**x**	**x**	**x**	**x**	**x**	**x**
*Coping with stress* (mini-COPE)	**x**	**x**	**x**	**x**	**x**	**x**
*Sensation seeking* (BSSS)	**x**	**x**	**x**	**x**	**x**	**x**
*Emotional regulation* (DERS)	**x**	**x**	**x**	**x**	**x**	**x**
*Impulsivity* (SUPPS)	**x**	**x**	**x**	**x**	**x**	**x**
*Life satisfaction* (SWLS)	**x**	**x**	**x**	**x**	**x**	**x**

EMA will be conducted daily to monitor cravings and lapses. The EMA will also record additional variables that are associated with craving intensity, such as current mood, arousal, stress, anxiety, loneliness, fatigue, anger, hunger, and uncertainty.

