### Data analysis

Factorial design mixed-effects models will be applied to compare questionnaire battery scores between experimental groups and the control across measurements. In addition, we will perform an interrupted time series analysis to estimate the effects of different types of interventions on longitudinal ecological momentary assessment outcomes.

In the statistical analysis, we will incorporate data from participants who have completed a minimum of 21 Ecological Momentary Assessment (EMA) entries, spread over the one-month period dedicated to evaluating the intervention. For the assessment of the intervention’s enduring effects, the analysis will consider participants who have logged at least three EMA entries during the follow-up phase. In addition, within the intervention group, we will include those who have accessed the app and engaged with the self-guided intervention modules on a minimum of four occasions and at least once, respectively; this will represent the minimal therapeutic exposure required for the study. For the analysis of secondary outcomes, we will include participants who have completed the initial baseline assessment as well as at least one subsequent follow-up assessment.

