Regarding the limitations of the study, we anticipate the potential for a high dropout rate, a common occurrence in previous studies (42) and a concern intrinsic to trials with a longitudinal design. Nonetheless, the inclusion of a contest as an engagement strategy is expected to enhance participant retention rates. It’s crucial to note that the opportunity to win prizes is independent of participants’ self-reported levels of craving or instances of lapses, thereby mitigating any potential bias in their responses.

Drop-out rates in mobile application studies on addiction can be high due to various factors, including lack of motivation, technical issues, limited support and guidance, loss of interest, or intervention design. Lack of adequate support, guidance, or encouragement from researchers or healthcare professionals throughout the study can diminish users’ motivation and commitment to using the application. Reducing dropout rates in mobile applications designed for addiction research requires a combination of strategies to increase engagement and enhance the intervention’s effectiveness. Behavioral tracking and personalized feedback can help users stay motivated and focused on their goals. We will use push notifications and reminders to prompt users to engage with the application regularly, complete tasks, or provide updates. We also provide educational materials and psychological intervention modules based on CBT and mindfulness techniques, which could increase the retention rate and provide support in coping with substance use disorder. We informed users at the beginning of the study that the application could not replace psychotherapy.

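### The 80% power figure rests on 360 participants, and recruiting about 400 leaves room for only about 10% total loss when high dropout is foreseen and analysis exclusions are planned

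*Protocol article*

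**What the plan says.** Four places in the protocol article bear on this.

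- **Sample size calculation.** "The simulation indicated that a minimum of 360 participants would be necessary to achieve an 80% power threshold for detecting a significant group effect". The simulation is described as "premised on the use of a linear mixed-effects model with subject-level random intercepts and a small effect size of the intervention". The effect size is not given as a number. Neither are the within-person correlation, the number of measurements, alpha or an attrition rate.
- **Participants.** "We plan on recruiting 150 participants with alcohol addiction, 150 participants with cross-addiction, and ~100 participants with cannabis addiction". That is about 400 in total.
- **Discussion (limitations).** "we anticipate the potential for a high dropout rate, a common occurrence in previous studies". No rate is attached. The same paragraph expects the prize contest to improve retention.
- **Data analysis.** The analysis will use "participants who have completed a minimum of 21 Ecological Momentary Assessment (EMA) entries, spread over the one-month period". In the intervention arm it will also be limited to those who "accessed the app and engaged with the self-guided intervention modules on a minimum of four occasions and at least once, respectively". Secondary outcomes have their own rule: a baseline assessment and at least one follow-up assessment.

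No section links the 360 to the 400 through an allowance for loss.

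**The concern.** A simulated minimum of 360 with no attrition among its named premises reads as the number needed in the analysis. The surplus of 40 recruits must then absorb every kind of loss: recruits who never log in (condition is assigned only at first login), dropouts, participants below the EMA threshold, and intervention participants below minimum use. The protocol foresees possibly high dropout and adds exclusions on top, so a surplus of that size looks thin.

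What is at stake is how a null result will be read. The protocol assumes a small effect and prepares readers for one, so a non-significant comparison is a real possibility. If it is judged against a stated 80% power that the analysed sample did not have, it will look like stronger evidence of no effect than it is.

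**Working it through.** **Inputs from the article.** 360 participants for 80% power (Sample size calculation); 150 + 150 + about 100 = about 400 recruited (Participants); at least 21 entries in one month of daily EMA (Data analysis; Measures).

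**Inputs assumed.** Two-sided alpha 0.05, 1:1 allocation, and the loss rates. The article gives none of these.

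**1. Can 360 be reproduced?** Not uniquely. For two means, total N = 4 × (1.960 + 0.842)² × v / d², rounded up per arm, where v = (1 + (m - 1)ρ)/m for m measurements with within-person correlation ρ.

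- One measurement (v = 1): d = 0.20 gives 786, d = 0.25 gives 504, d = 0.30 gives 350.
- d = 0.20, m = 4, ρ = 0.3: v = 0.475, N = 374.
- d = 0.20, m = 30: ρ = 0.4 gives 330 and ρ = 0.5 gives 406.

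So 360 is attainable under plausible unstated inputs. It is neither confirmed nor refuted, and it is taken as given below.

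**2. Tolerable loss.** 1 - 360/400 = 10.0%. Since the cannabis target is approximate, 1 - 360/390 = 7.7% and 1 - 360/410 = 12.2% bracket it. Seen from the other side, 40/360 = 11.1% is the surplus over the minimum.

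**3. Power at smaller numbers.** Anchoring on 80% at 360, the noncentrality is 2.802 × √(N/360) and power = Φ(noncentrality - 1.960). The implied standardised effect on the participant mean is 2.802 × √(4/360) = 0.295. The last column is 360/(1 - loss).

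| Total loss from 400 | Analysed | Power | Recruits needed to keep 360 |
|---|---|---|---|
| 0% | 400 | 84.0% | 360 |
| 10% | 360 | 80.0% | 400 |
| 15% | 340 | 77.7% | 424 |
| 20% | 320 | 75.2% | 450 |
| 30% | 280 | 69.5% | 515 |
| 40% | 240 | 62.8% | 600 |
| 50% | 200 | 55.1% | 720 |

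The use criterion applies to one arm only. Unequal losses would lower these figures slightly further.

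**4. The EMA threshold.** 21/30 = 70% of daily prompts (75% of 28 days, 68% of 31). This is a completion threshold for each participant. The article does not say how many will miss it.

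**5. Would relaxing the exclusions restore power?** Not necessarily. As an illustration, suppose 30% of the intervention arm never use a module and gain nothing.

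- All 400 analysed, effect diluted to 0.7: 2.802 × √(400/360) × 0.7 = 2.07, power about 54%.
- Non-users excluded (140 v 200): effective N = 4 × 140 × 200/340 = 329.4; 2.802 × √(329.4/360) = 2.68, power about 76%.

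**The case against.** The strongest reply is that the article never says 360 must be analysed. It says participants, it condenses a fuller plan, and it points to a pre-registration not shown here. A simulation with missing data built in cannot be ruled out. That stands as a limit on certainty. It does not remove the point, because the section names its premises and attrition is not one of them. If attrition was included, one sentence settles the matter.

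It is also fair to say that recruitment exceeds the stated minimum, that reminders and a contest are planned, and that dropout is openly listed as a limitation. This also stands: the shortfall is conditional on the loss.

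A third reply is that the EMA exclusion may not touch the powered model. The Data analysis section assigns mixed-effects models to questionnaire scores and interrupted time series to EMA outcomes, while the power calculation uses a mixed-effects model. This is a genuine ambiguity, and it is itself a reason to state which outcome the 360 covers. A mixed model would ordinarily keep partial completers, but where the 21-entry rule applies it removes them entirely.

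Several stronger readings are tempting and not supported:

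- *The trial is underpowered by its own expectations.* The Discussion speaks of a potential for high dropout and gives no rate, so only the conditional statement follows.
- *The 70% threshold means 30% will be lost.* It is a threshold per participant, not a forecast.
- *Even 360 analysed gives only 71%.* That is Φ(2.802 - 2.241), which assumes alpha split across the two primary outcomes. The article states no such rule.
- *Dropping the exclusions recovers power at no cost.* Including non-users can dilute the effect, as the illustration shows.

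**Conclusion.** The point holds in conditional form. Taking 360 as the number needed in the analysis, which is the most natural reading but an inference, 80% power survives only if all losses together stay within about 10% of those recruited (7.7% to 12.2% given the approximate total). With possibly high dropout foreseen and further exclusions planned, that is doubtful.

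The break-even follows from the article's own numbers. The size of any shortfall does not, because no loss rate is given: under the stated assumptions power moves from about 84% with nobody lost to about 63% at 40% loss and 55% at 50%. The 360 itself is not shown to be wrong. The defect is that the power statement is not tied to the number the plan is likely to analyse, nor to a named primary outcome. One primary outcome, the number of lapses, is a count that a linear model does not obviously cover.

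**What to change.** 1. State whether 360 means recruited or analysed, and which primary outcome it covers.
2. Rerun the existing simulation with the expected attrition and the Data analysis exclusions, giving the assumed loss rate, alpha and allocation ratio.
3. Restate the power, or the detectable effect, at the expected analysed number, separately for craving and for the lapse count.

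This costs one rerun and a revised paragraph, and the figure will probably be less favourable. No extra patients are needed.

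Separately, consider making the primary analysis one of all randomised participants with available EMA data, and keeping the set defined by 21 entries and minimum use as a sensitivity analysis. The reason is bias: the present rules select participants after randomisation, and the use criterion falls on one arm only. The cost is possible dilution of the effect, so the change should not be presented as a free gain in power.
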